# Saving Little Lives Minimum Care Package Interventions in 290 Public Health Facilities in Ethiopia: Protocol for a Non-Randomized Stepped-Wedge Cluster Implementation Trial

**DOI:** 10.3390/children13020187

**Published:** 2026-01-29

**Keywords:** neonatal mortality, prematurity, low birth weight, birth asphyxia, neonatal infections

## Abstract

Background: Neonatal mortality remains a significant public health challenge in Ethiopia. Despite efforts to implement key evidence-based interventions, their coverage and utilization remain low. The Saving Little Lives (SLL) program aims to scale-up a Minimum Care Package (MCP) of synergistic, life-saving interventions for all liveborn neonates, with a focus on preterm and low birth weight (LBW) infants, across 290 hospitals in Ethiopia (206 primary, 69 general, and 15 referral hospitals), representing 82% of all hospitals in the country at the time of the study, and evaluate the impact on neonatal mortality. Methods: A non-randomized stepped-wedge trial will be conducted to evaluate the impact of implementing the SLL MCP interventions. Quantitative evaluation data will be collected from 36 primary hospitals, selected from 206 primary hospitals across four regions, receiving the interventions. An independent evaluation research assistant will be deployed in each of the hospitals to collect data using Open Data Kit (ODK) through interviewing mothers before discharge, on the 29th day of life if discharged, and reviewing medical records. A mixed-method, cross-sectional formative assessment will be conducted prior to implementation, employing quantitative facility assessment and qualitative interviews with mothers, healthcare providers, and facility managers. This will be followed by continuous program learning assessment once implementation begins. Descriptive data will be presented using numbers, percentages, tables, and graphs. Regression modeling and generalized estimating equations (GEEs) will be used to estimate the impact of the SLL MCP interventions. Qualitative data will be gathered through in-depth interviews, digitally recorded, transcribed, and thematically analyzed using ATLAS.ti Version 7.5 software to assess facility readiness, barriers, and enablers of implementing the SLL MCP interventions. Expected Outcome: We hypothesize that achieving 80% coverage of the SLL MCP interventions among eligible neonates will result in a 35% reduction in neonatal mortality at implementation facilities.

## 1. Introduction

Despite significant global progress in reducing under-five child mortality over the past two decades, neonatal deaths have remained steady, accounting for 47% of total under-five deaths in 2022. Of the 2.3 million neonatal deaths every year, 46% occur in sub-Saharan Africa [1]. With an estimated 33 neonatal deaths per 1000 live births in 2019, Ethiopia is far from meeting United Nations Sustainable Development Goal (SDG) 3.2.2 of achieving less than 12 neonatal deaths per 1000 live births [1]. Complications due to prematurity, infection, and birth asphyxia contribute to more than 74% of neonatal deaths [2], and about 80% of neonatal deaths occur among preterm (born before 37 weeks of gestation) or low birth weight (born with less than 2500 g weight) newborns [3]. Among premature neonates, deaths are mostly due to respiratory distress syndrome (RDS) (45%), infection (30%), and birth asphyxia (13%) [4]. Hence, evidence for strategies to effectively identify and manage drivers of neonatal morbidity and mortality are critically needed to promote neonatal survival.

A considerable number of contributors to neonatal mortality are preventable through the effective implementation of existing evidence-based interventions. Investments in ensuring quality maternity and newborn care at hospitals, making infrastructure and device bundles available in Neonatal Intensive Care Units (NICUs), and implementing infection prevention measures are crucial to accelerating progress toward SDG goals for ending preventable deaths globally [5]. The World Health Organization (WHO) recommends continuous positive airway pressure (CPAP) to manage respiratory distress syndrome (RDS) in preterm newborns [6]. Infection prevention and management of sepsis using antibiotics are also key interventions to prevent neonatal deaths caused by infection [6,7]. A significant proportion of deaths due to birth asphyxia can be avoided through timely and efficient bag-mask ventilation after birth [8]. Other evidence-based interventions include antenatal corticosteroids for pregnant mothers at imminent risk of preterm birth [9,10], and Kangaroo Mother Care (KMC) for preterm and low birth weight (LBW) newborns [6]. In addition, improving feeding practices among preterm and LBW newborns can reduce the risk of neonatal death, up to 45% of which is attributed to malnutrition [11].

The Ethiopian Newborn and Child Survival and Development Strategy prioritizes antenatal corticosteroids for preterm labor, neonatal resuscitation and respiratory support, KMC, antibiotics for neonatal sepsis, and early initiation and exclusive breastfeeding as key interventions to improve neonatal survival [7]. Furthermore, Ethiopia has been making substantial national investments to improve neonatal care across the health system, as articulated in strategic documents, strategies, and guidelines [12,13]. These strategy documents provide guidance for achieving a substantial reduction in neonatal mortality (to 21 deaths per 1000 live births) by 2025 [14]. However, Ethiopia remains among the five countries with the highest neonatal mortality rates [1]. More importantly, the coverage of key interventions remains low, resulting in high neonatal mortality rates.

Building on the lessons learned from the successful scale-up of KMC implementation research conducted in collaboration with the WHO to scale up KMC in four major regions of the country between 2016 and 2019 [15], the SLL MCP program aims to scale up lifesaving interventions for eligible liveborn infants, with a focus on preterm and LBW newborns. We hypothesized that the estimated mortality reduction target will be met by achieving 80% coverage of an evidence-based bundle of interventions for eligible neonates during childbirth, in the NICU, and in the KMC unit, with a focus on preterm and LBW newborns, in 290 hospitals across four regions in Ethiopia over a three-year implementation period. Given that the hospitals covered by the SLL MCP program represent 82% of the total 353 hospitals operating in the country [16], and in accordance with the government’s strategy for comprehensive newborn care and leveraging the existing structures of the national and regional health system, led by the government, the objective of this project is to reduce neonatal mortality by 35% in the implementation centers, measuring the coverage and impact of implementing the SLL MCP interventions on neonatal mortality.

## 2. Materials and Methods

### 2.1. Setting

Ethiopia is a federal republic. At the time of protocol development, the country was administratively divided into nine regions (the highest level of administrative division), 66 zones (intermediate administrative division), and 670 woredas (the third level and basic unit of local government, responsible for service delivery and governance at the community level). Ethiopia has a three-tier service delivery system. The primary level of care consists of primary hospitals, health centers, and health posts, each serving a population of 60,000–100,000. The secondary level of care comprises general hospitals, each serving a catchment population of 1,000,000–1,500,000. The tertiary level of care is composed of referral and specialized hospitals, each serving a catchment population of 3,500,000–5,000,000 [12].

The SLL MCP interventions will be implemented in 290 hospitals across four regions in Ethiopia: Oromia, Amhara, Tigray, and Southern Nations, Nationalities, and People (SNNP). These four regions are home to more than 85% of the country’s population (estimated 84.6 million). According to the Central Statistics Agency’s 2019 population projection, Ethiopia’s total population was estimated at 98.7 million [17]. The latest UNESCO report indicates that the literacy rate among individuals aged 15 and above in Ethiopia is 52% (59% for males and 44% for females). Table 1 provides a summary of the estimated population, annual total births, annual <2500 g births, annual <2000 g births, and annual preterm births in the catchment woredas of SLL-supported hospitals.

### 2.2. Study Design

We will conduct a non-randomized stepped-wedge implementation study from 1 June 2021 to 30 May 2024 (Table 2).

The implementation of the SLL MCP interventions will be carried out in three phases, with SLL-supported hospitals intentionally selected in these phases. In phase one, intervention facilities adjacent to the scale-up KMC implementation research sites will be chosen in collaboration with regional health bureaus to maximize skill transfer from facilities involved in the KMC scale-up implementation research to new SLL facilities [15]. In phases two and three, sites will be enrolled based on their proximity to phase one hospitals to facilitate the diffusion of skills and experience. Eventually, all targeted facilities will receive the SLL MCP interventions. Because the intervention timing is sequential and evaluation data will be collected throughout the project across all evaluation sites, each facility will participate in both the intervention and comparison periods. This approach is assumed to enhance the statistical power to assess the interventions’ effect.

To evaluate the coverage and impact of the SLL MCP interventions, 36 primary hospitals will be randomly selected from the total 206 primary hospitals across the four regions receiving the SLL MCP interventions over the three implementation cycles. General and referral hospitals are excluded from the sample because the project aims to evaluate the impact of the SLL MCP interventions at the lowest level of hospitals in the health system where the interventions are most needed. After the primary hospitals that will receive the interventions in the first, second, and third phases are identified in collaboration with the regional health bureaus, the 36 evaluation sites will be randomly selected, with 12 from each implementation cycle and 9 from each of the four regions.

Additionally, the study will conduct a mixed-method cross-sectional formative assessment using qualitative and quantitative data collection tools from the hospitals at the beginning of each implementation phase. The assessment aims to assess the readiness of the facilities to implement the SLL MCP interventions and identify contextual barriers and facilitators to the implementation of the SLL MCP interventions. To guide the formative assessment, we adapted the Consolidated Framework for Implementation Research (CFIR).

During the implementation of the SLL MCP interventions, ongoing assessment of program learning will be conducted, following the CFIR domains, to generate learning through the continuous collection and analysis of qualitative data, which will be used throughout the study to improve implementation performance.

Furthermore, the project will conduct incremental cost analysis for implementing the SLL MCP interventions at the evaluation hospitals. The proposed approach focuses on estimating the cost effectiveness (one-time fixed costs and recurring costs at each phase of scale-up) of the SLL MCP project. Intervention activities will be costed at the (a) project level and (b) health facility level. A micro-costing approach will be adopted to include a bottom–up construction of costs associated with integrating the SLL MCP interventions into the current practice. With such an ingredient costing approach, costs will be determined whereby actions to be taken under scale up of the SLL MCP interventions are listed, additional specific resources needed to implement the interventions are described, and prices are assigned for all the resources based on opportunity costs, as well as based on financial records and from interviews with program managers.

Table 3 summarizes the study components in this project, the type of statistical evaluation, the target population, and the data collection in each case.

### 2.3. Study Participants

The SLL MCP interventions will target all mother–neonate dyads, but will most benefit preterm and LBW newborns who are at highest risk of dying in the first month of life. To measure the impact of the SLL MCP interventions, all live births and newborns who receive care at the 36 evaluation primary hospitals are eligible for inclusion in the study. Mothers who have stillbirths will be excluded as their stillborn is not eligible to receive the SLL MCP interventions, most of which is provided starting immediately after birth.

In addition, the study will include health facility administrators, healthcare providers, mothers giving birth in hospitals and their families, and mothers and their families whose newborns are admitted to NICU and KMC units, with the goal of gathering information on the care experience of administrators and providers and on the care received by mothers and their families, especially those with premature and low birth weight newborns.

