### 2.4. SLL MCP Intervention Packages

The SLL MCP interventions aim to enhance care quality for all neonates, particularly focusing on the most vulnerable small and preterm newborns, by strengthening hospitals’ ability to manage these vulnerable newborns. The SLL MCP interventions will implement a low-dose high-frequency clinical mentorship model [18] to build the competency and confidence of healthcare providers in labor and delivery, NICU, and KMC units in care provision for all neonates, with a special focus on small and preterm babies who are at risk of a range of complications.

To achieve the project’s set goal of neonatal mortality reduction, the SLL MCP interventions address three point-of-care areas: (i) labor and delivery, (ii) NICU, and (iii) KMC units. The SLL MCP package in the labor and delivery unit includes preparation for birth (confirming essential supplies such as magnesium sulphate, antibiotics, sanitizers are available, birth companion identified and prepared, delivery room is cleaned and warmed, and delivery kits prepared), essential newborn care components including resuscitation for asphyxiated newborns, CPAP at labor and delivery, prevention of infection, thermal care, early initiation and exclusive breastfeeding, and safe referral (provide pre-referral treatment, inform family on referral, prepare referral note, identify provider to accompany the newborn during referral, and arrange emergency transport service) of small and sick neonates. The SLL MCP intervention package in the NICU includes care recommendations for the level of the facility, such as management of bacterial infections including sepsis, CPAP for RDS, thermal care, and feeding management. The KMC care package consists of exclusive breastfeeding and skin-to-skin care for at least 8 h per day in line with WHO recommendations (See Figure 1).

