### 2.5. Implementation Strategy

At the hospital level (Figure 2), all newborns at SLL MCP implementation hospitals will receive care immediately after birth, which includes preparing for and providing clean and safe childbirth care. During the intrapartum period, maternal and fetal statuses will be monitored, and complications will be managed, including resuscitation for asphyxiated newborns, prevention of infection, thermal care, and breastfeeding initiation. Maternal and neonatal care will continue at the postnatal care unit for 24–48 h until the mother is discharged.

Newborns will be screened for any complications. Small and/or sick newborns in need of additional and supportive care will be linked with or referred to an appropriate care facility or unit. Newborns who have complications such as RDS, sepsis, or other complications will be admitted to the NICU and receive appropriate care. Newborns who weigh less than 2000 g at birth and who are stable will be transferred to the KMC unit for continuous KMC, which includes prolonged skin-to-skin care and exclusive breastfeeding until they meet the discharge criteria (Figure 1).

Guided by the Institute for Healthcare Improvement (IHI) framework for innovation spread, the national quality strategy, and WHO maternal and newborn health quality standards, we will develop/adapt and use care at birth, NICU, and KMC quality standards, verification criteria, and assessment tools by aligning WHO recommendations with national guidelines and protocols to continuously assess the input, process, and output performance of the implementation facilities and sites. We will adapt Plan–Do–Study–Act (PDSA) continuous quality improvement cycles to use the data from quality assessments and root cause analysis using tools such as fish bone diagrams and program implementation learning to refine the implementation and improve the performance of SLL MCP implementation.

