### 2.6. Sample Size Estimation

While the SLL MCP interventions will be implemented in 290 hospitals consisting of primary, general, and referral hospitals, only live births and newborns treated in primary hospitals will be included and followed until their 29th day of life to estimate the impact of the intervention on neonatal mortality.

To estimate the impact of the SLL MCP interventions on neonatal mortality, the sample size required to detect a 35% reduction in neonatal mortality after implementation of the SLL MCP interventions is calculated using a sample size calculator for a stepped-wedge design. Assuming that a woreda will have a minimum population of 30,000, and with a conservative estimate of a crude birth rate of 20 births per 1000 population, there will be a minimum of 600 births per cluster (woreda) in a year. We estimated the sample size using an online sample size calculator for a stepped-wedge design (https://clusterrcts.shinyapps.io/rshinyapp/, Accessed on: 13 May 2021), considering a cross-sectional sampling structure, a discrete time decay correlation structure, 3 sequences, 0.02 ICC, and 0.8 cluster autocorrelation. The neonatal mortality under control and intervention conditions was considered to be 33 and 22 per 1000 live births, respectively, with 80% power and a 5% level of significance. The sample size required to detect a 35% reduction in neonatal mortality in the implementation sites is 12 clusters per sequence (36 clusters overall). At each phase of SLL MCP implementation, an estimated 21,600 newborns across the four implementation regions will be screened to assess neonatal outcomes.

An SLL MCP cluster will be a primary hospital that covers a woreda with an estimated minimum population of 30,000. Typically, a woreda has one primary hospital with referral linkage to a general and a referral hospital. In this evaluation design, we will progressively roll out the interventions by cluster. From the 286 woredas, the impact of the SLL MCP interventions will be measured in 36 selected woredas, hereafter referred to as evaluation clusters (9 clusters per region).

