### 2.7. Data Management

#### 2.7.1. Data Collection Procedure and Tool

Quantitative impact evaluation data will be collected from 36 evaluation sites. Evaluation research assistants (ERAs) with experience working at the NICU will be trained and deployed at the selected evaluation sites to generate data for all live births. The ERAs will enroll and interview mothers at labor and delivery, NICU, and KMC units. In addition, they will extract data from patient charts and registers and make phone calls to parents of each baby on the 29th day of life to follow up on the survival status of the neonate.

To complement the evaluation data generated by the ERAs and understand the patterns and trends of neonatal mortality at the hospitals, before and after SLL MCP implementation, data will also be extracted from the District Health Information System (DHIS2) and logbooks of SLL-supported hospitals. A data extraction tool covering key variables from labor and delivery as well as NICU logbooks will be developed and used.

The mixed-method formative assessments will generate qualitative and quantitative data from managers, healthcare providers, and mothers who give birth at the hospitals and mothers with a newborn/s admitted to NICU and KMC units through in-depth interviews and observations. To guide the development of formative assessments and continuous program learning data collection tools, we adapted the CFIR [19,20]. Facility readiness will be assessed using the World Health Organization’s Service Availability and Readiness Assessment tool. Guided by the CFIR, we will develop in-depth interview guides tailored to the study participant groups.

The process and outcomes of implementing the SLL MCP interventions will be continuously monitored after the interventions are introduced. Monitoring will be accomplished using the government routine data from DHIS2 and independent data that the project evaluation research assistants and program learning team will collect from a sub-sample of users, care providers, and health facilities.

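### Stillbirths are left out of an evaluation whose package acts in labour and at resuscitation, so being counted as a live birth can depend on the intervention and deaths per 1000 live births can be biased

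*Protocol article*

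**What the plan says.** Section 2.3 defines the evaluation population: "all live births and newborns who receive care at the 36 evaluation primary hospitals are eligible for inclusion in the study". It then sets out the exclusion: "Mothers who have stillbirths will be excluded as their stillborn is not eligible to receive the SLL MCP interventions". The sentence ends with a qualifier about the package, "most of which is provided starting immediately after birth".

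Section 2.4 describes what is delivered: "the SLL MCP interventions address three point-of-care areas: (i) labor and delivery, (ii) NICU, and (iii) KMC units". The labour and delivery part covers preparation for birth and "essential newborn care components including resuscitation for asphyxiated newborns, CPAP at labor and delivery". Section 2.5 adds care before birth: "During the intrapartum period, maternal and fetal statuses will be monitored, and complications will be managed, including resuscitation for asphyxiated newborns".

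Data capture follows the same boundary. Under Section 2.7.1 the research assistants "will be trained and deployed at the selected evaluation sites to generate data for all live births". The planning rates in Section 2.6 are also per live birth: neonatal mortality "was considered to be 33 and 22 per 1000 live births, respectively, with 80% power and a 5% level of significance". The limitations section does not mention that the package might change which births are recorded as live.

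**The concern.** The outcome is a ratio whose denominator is defined by live birth. If the package affects whether a baby is recorded as live-born, that denominator is fixed after the intervention has begun to act, and part of the numerator with it. There are two routes.

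- **Rescue.** Better care in labour, or effective resuscitation, turns some would-be stillbirths into live births. These babies are likely to be at higher risk than other newborns, so they raise mortality per live birth in intervention periods only. A true benefit is then understated.
- **Classification.** A baby who shows no clear breathing and dies within minutes may be recorded as a stillbirth or as an early neonatal death. If that practice changes with the intervention, the rate moves although no outcome has changed. The direction depends on which way recording shifts.

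The regression adjustment and GEE in Section 2.7.4 deal with measured covariates and clustering. Neither corrects for selection into the denominator. At stake are bias in the main effect estimate and some loss of power.

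**Working it through.** **1. Side by side.** Section 2.3 rests the exclusion on stillborn babies being unable to receive the package. In Section 2.5, mothers and fetuses in labour are monitored and complications managed, so a fetus that dies in labour in an intervention period may already have been exposed. In Sections 2.4 and 2.5, resuscitation is given to asphyxiated newborns, which is exactly where live birth and stillbirth meet. The qualifier in Section 2.3 itself concedes that part of the package comes before birth.

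**2. The plan's own figure.** Inputs from Section 2.6: 33 and 22 per 1000, 3 sequences, 12 clusters per sequence, ICC 0.02, cluster autocorrelation 0.8 with discrete-time decay, 5% significance. Assumed: a standard 4-period layout, 600 births per cluster-period, a two-sided test. Generalised least squares on cluster-period means gives power 0.831 (normal reference) or 0.806 (t reference). Twelve per sequence is the smallest number that reaches 80%, so the stated 36 clusters reproduce. The planned reduction is 1 − 22/33 = 33.3%.

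**3. Rescue.** Let k be the extra live births per 1000 and q their risk of neonatal death. Neither is in the document. As an assumption, 10 to 20 fresh stillbirths per 1000 births with 10 to 20% becoming live births gives k = 1 to 4; q is taken as 0.5 to 0.7.

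Observed intervention rate = 1000 × (22 + kq) / (1000 + k)

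| k | q | Rate per 1000 | Apparent reduction from 33 | Power, 36 clusters (normal) |
|---|---|---|---|---|
| 0 | – | 22.0 | 33.3% | 0.83 |
| 1 | 0.5 | 22.5/1001 → 22.5 | 31.9% | 0.79 |
| 4 | 0.5 | 24.0/1004 → 23.9 | 27.6% | 0.66 |
| 4 | 0.7 | 24.8/1004 → 24.7 | 25.1% | 0.58 |

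If q equals 22 per 1000, there is no shift.

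**4. Other assumptions.** Let s be stillbirths per 1000 total births under routine care and f the share that become live births:

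Rate = 1000 × [(1000 − s) × 0.022 + s·f·q] / [(1000 − s) + s·f]

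With s = 15 to 40, f = 0.1 to 0.3 and q = 0.1 to 0.5, the rate runs from 22.1 to 27.9 and the apparent reduction from 33.0% down to 15.5%. A middle case (s = 25, f = 0.2, q = 0.3) gives (21.45 + 1.5)/(975 + 5) = 23.4 per 1000, a 29.0% reduction and power 0.71.

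**5. Classification.** If k early deaths per 1000 live births are recorded as stillbirths, with no true effect, the rate is 1000 × (33 − k)/(1000 − k). For k = 1, 2, 3 this is 32.0, 31.1 and 30.1, a spurious reduction of 2.9%, 5.9% and 8.8%. The reverse change, with babies formerly called stillborn now recorded as neonatal deaths (q = 1), raises the rate: with s = 15 and f = 0.05 it becomes 22.7 instead of 22.

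**6. An outcome that does not depend on the boundary.** Stillbirths plus neonatal deaths per 1000 total births, in the middle case of step 4:

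- Routine care: 25 + 975 × 0.033 = 57.2
- Intervention: 25 × 0.8 + 975 × 0.022 + 25 × 0.2 × 0.3 = 20 + 21.45 + 1.5 = 43.0

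That is a 24.9% fall. A pure change of label leaves the count untouched, and a rescued baby who survives counts as a gain.

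**The case against.** - **Deaths per live birth is the usual definition of neonatal mortality.** This stands, and the primary outcome should remain.
- **The reason in Section 2.3 is qualified.** The sentence says only that most of the package starts after birth. It is therefore incomplete rather than flatly contradicted. But the qualifier also admits the earlier exposure that the exclusion sets aside.
- **The care before birth is thin.** Section 2.4 does not list fetal monitoring; it appears in one sentence of Section 2.5, where most of the care named is for the newborn. This weakens the rescue route through labour care. Resuscitation remains a clear route.
- **Stillbirths might still be visible.** Section 2.7.1 plans extraction from DHIS2 and from labour and delivery logbooks before and after implementation. A reader might infer that the bias can never be checked. The article does not support that: stillbirth counts are neither named among the extracted variables nor ruled out.
- **Nothing shows that recording would change.** The evaluation data come from independent research assistants, and no text suggests that mentored units relabel deaths. This route is a possibility only.

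Two stronger readings are tempting. One is that a real gain could look like harm. In every case computed above the intervention still shows a reduction. The other is that reclassification alone could deliver the 35% target. The largest spurious reduction above is 8.8%.

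**Conclusion.** The point holds as a possible bias, not a demonstrated one. Live-birth status can depend on the intervention, the planned adjustment does not address this, and the limitations section does not acknowledge it. With 1 to 4 extra high-risk live births per 1000 and 50 to 70% of them dying, the observed rate would be about 22.5 to 24.7 instead of 22, and the apparent reduction about 25 to 32% instead of 33.3%. Power would fall from about 0.83 to between 0.79 and 0.58. The design has little slack to absorb that, since 12 clusters per sequence only just reaches 80%. All these sizes rest on assumed values. The shift would be nil if rescued babies died at the ordinary rate, and a change in classification could act either way.

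**What to change.** 1. Keep neonatal mortality among live births as the primary outcome. In Section 2.3, remove the stated reason or correct it to say that part of the package acts before and at birth.
2. Capture stillbirth counts at the 36 hospitals for all periods from the labour and delivery registers: date, birth weight, fresh or macerated. The stated study period ended in May 2024, so where prospective logging is no longer possible this means retrospective extraction.
3. Report the stillbirth rate by intervention status.
4. Pre-specify one supporting outcome on the same model: all stillbirths plus neonatal deaths per 1000 total births. Use a fresh-stillbirth version only as a sensitivity analysis, because mentoring could itself change the fresh or macerated label.
5. Add a sentence to the limitations section.

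The cost is a short register form without a maternal interview, alongside register review and logbook extraction that are already planned, and one extra model. The drawbacks are imperfect register quality and a supporting outcome diluted by antepartum stillbirths that the package cannot affect.
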